##### Statistical analysis

The primary endpoint will be compared between the two groups using a two-sample *t*-test or non-parametric Mann–Whitney test, depending on distribution of the composite scores. The primary analysis will be by intention-to-treat, including all patients with 12 month MDADI data. A p-value of <0.05 will be considered statistically significant. Analysis of covariance (ANCOVA) will be used to investigate other patient and clinical factors that could be associated with change in MDADI composite score from baseline to 12 months post- treatment. Chi-squared or Fisher’s exact test will be used to compare patients in both groups with deterioration of 10 points or more in the MDADI composite score.

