#### Patient population

Patients should satisfy all the inclusion criteria and meet none of the exclusion criteria specified in Table 1 to be eligible for the trial. In brief, patients will have biopsy proven, pharyngeal cancers that will be treated with bilateral neck irradiation. The use of both prophylactic and reactive feeding tube insertions is acceptable, though patients would be encouraged to keep swallowing (even if very limited amounts) for the duration of treatment.

**Table 1 Tab1:** Inclusion and exclusion criteria for patient recruitment in the DARS trial

ᅟ	ᅟ
Inclusion Criteria:	
• Aged 18 or above;	
• Any patient undergoing radiotherapy for HNC in the oropharynx or hypopharynx. Patients with tumour at other sites where radical radiotherapy dose is to be delivered to the pharyngeal constrictors may also be eligible;	
• Stage T1-4, N0-3, M0 disease; this will be mostly histologically confirmed squamous cell carcinoma but other histological types may be eligible;	
• Radiotherapy with concomitant chemotherapy (unless contraindicated) is the planned treatment;	
• Creatinine clearance (≥50 mL/min prior to starting chemotherapy); not applicable for patients receiving radiotherapy alone;	
• WHO performance status 0 or 1;	
• Available to attend long term follow- up;	
• Adequate cognitive ability to complete the MD Anderson Dysphagia Inventory (MDADI), University of Washington Quality of Life (UW-QoL) v.04 questionnaire and Performance Status Scale for Head & Neck Cancer (PSS-HN) assessments;	
• Written informed consent.	
Exclusion Criteria:	
• Documented evidence of pre-existing swallowing dysfunction (not related to HNC);	
• Previous radiotherapy to the head and neck region;	
• Posterior pharyngeal wall, post- cricoid and retropharyngeal lymph node involvement;	
• Lateralised tumours, requiring unilateral irradiation	
• Major head and neck surgery (excluding biopsies/tonsillectomy);	
• Current/previous tracheostomy placement;	
• Previous or concurrent illness, which in the investigator’s opinion would interfere with completion of therapy, trial assessments or follow-up;	
• Any invasive malignancy within previous 2 years (other than non-melanomatous skin carcinoma or cervical carcinoma in situ).	

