#### Study objectives and endpoints

The primary objective of the DARS trial is to determine whether reducing the radiation dose to DARS using Do-IMRT, improves swallowing function compared to S-IMRT in pharyngeal cancer patients treated with radical chemoradiation or radiation alone. The impact of the dosimetric sparing achieved with Do-IMRT on late swallowing function will be evaluated by a patient-reported outcome (PRO) using the MDADI. The difference in the mean MDADI composite score at 12 months after treatment completion between randomised treatment groups forms the primary endpoint of the trial.

Secondary objectives are to:Investigate the longitudinal pattern of patient-reported swallowing function up to 2 years post- radiotherapy treatment using the MDADI;Investigate the impact of using Do-IMRT on(i)normalcy of diet and public eating using the PSS-HN scale;(ii)swallowing performance using the 100 mL Water Swallow Test and VF examination (subset of centres only);(iii)acute and late toxicity(iv)duration of feeding tube use;
Assess patient-reported QoL and priority concerns using the UW-QoL questionnaire (v.04);Compare cancer- related outcomes according to radiotherapy technique used, including resection rates, location and timing of loco-regional recurrence and overall survival.

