#### Registration/randomisation

The trial has a two-stage entry process of registration and randomisation. Randomisation only occurs following target outlining, ensuring consistency across both the experimental and standard treatment volumes by avoiding any potential bias that could be introduced by the clinician during delineation. Additionally, patients and SLTs will be blinded to the treatment allocation to avoid bias during assessments. This is particularly relevant in a trial of this nature where a majority of endpoints rely on a combination of patient- reported outcomes and SLT- led evaluations.

Patients will be randomised between the 2 treatments on a 1:1 basis using the method of minimisation with a random element. Randomisation will be performed centrally by the Institute of Cancer Research Clinical Trials Statistics Unit (ICR-CTSU). Patients will be stratified prior to randomisation by centre, use of induction and concomitant chemotherapy, tumour site (incorporating HPV status for oropharyngeal tumours) and American Joint Committee on Cancer (AJCC) tumour stage.

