##### Swallowing assessments

A panel of subjective and objective swallowing outcome measures (Table 2) will assess swallow function at regular intervals.

**Table 2 Tab2:** Functional measures and endpoints

Time point	Study	Domain	Endpoint
Baseline, 3, 6, 12, 18 and 24 months	MDADI	Swallowing related QoL	Composite (total), global, emotional, functional and physical subscale scores
Baseline, 3, 6, 12, 18 and 24 months	WST	Swallow Performance	Swallow capacity, Swallow volume
Baseline, 12 and 24 months	VF^a^	Airway protection	Penetration Aspiration Scale [52]
Baseline, 12 and 24 months	VF^a^	Physiology	MBSImp
Baseline, 12 and 24 months	VF^a^	Pharyngeal dysphagia grade	DIGEST grade [53]
Baseline, 3, 6, 12, 18 and 24 months	PSS-HN	Functional Performance Status	Normalcy of diet, eating in public, understandability of speech scores
Baseline, 3, 6, 12, 18 and 24 months	UW-Qol v.04	HR-QoL	Composite scores of physical and social-emotional functioning are derived from 12 domains. Patients can also highlight up to 3 priority concerns from the previous 7 days

Abbreviations: *WST* Water Swallowing Test, *DIGEST* Dynamic Imaging Grade of Swallowing Toxicity, *MBSImp* Modified Barium Swallow Impairment Profile

^a^Subset of centres only

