## Discussion

The DARS trial is, to the best of our knowledge, the first RCT aiming to demonstrate that reducing the radiation dose to critical swallowing structures can safely improve long- term swallowing function and quality of life. The DARS trial design represents the efforts of a successful collaboration between UK H&N oncologists, physicists, clinical trialists, and SLTs, particularly within the context of a H&N primary CRT trial. Additionally, the association between clinicians and SLTs, both in DARS and the currently recruiting PATHOS trial, has huge potential for the future integration of routine swallowing outcome measures into UK clinical practice for patients with HNC. The trial methodology reflects the necessity to minimise confounding factors that might affect the robustness of its final results. Excluding patients with pre-existing dysphagia ensures that any post- treatment swallowing dysfunction is as a result of (chemo)-radiation treatment alone. Likewise, patients with posterior pharyngeal wall tumours are ineligible for the trial as any meaningful sparing of the PCM is unlikely to be achievable. By being selective in our approach, the trial is better equipped to determine the effectiveness of Do-IMRT across a homogeneous group of pharyngeal cancer patients. Defining the most accurate time point for long-term dysphagia remains controversial within the context of a clinical trial. Swallow sparing studies have so far adopted various time points ranging from 3 to 12 months following completion of treatment [4, 28, 36, 42]. While 3 months is clearly too early to assess long-term functional outcomes, patterns of swallowing function can change between 6 and 12 months with stabilisation thereafter [4, 43], suggesting that the 12- month timeline from treatment completion is more likely to be predictive of subsequent dysphagia.

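### The primary comparison of 12-month MDADI is fixed as an unadjusted two-sample test; adjusting for baseline MDADI and the minimisation factors would gain precision at no cost in patients

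*Protocol article*

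**What the plan says.** - **Endpoint** (Protocol article, Study objectives and endpoints): "The difference in the mean MDADI composite score at 12 months after treatment completion between randomised treatment groups forms the primary endpoint".
- **Primary test** (Statistical analysis): "The primary endpoint will be compared between the two groups using a two-sample" t-test or a Mann–Whitney test, depending on the distribution of the scores, by intention to treat in patients with 12-month data. No covariate is named.
- **ANCOVA** (same section): it "will be used to investigate other patient and clinical factors that could be associated with change in MDADI composite score from baseline to 12 months" after treatment. That is a search for other factors related to change, not the primary treatment comparison.
- **Allocation** (Registration/randomisation): 1:1 minimisation with a random element. "Patients will be stratified prior to randomisation by centre, use of induction and concomitant chemotherapy, tumour site" (with HPV status for oropharyngeal tumours) and AJCC stage.
- **Baseline score** (Swallowing assessments, Table 2): MDADI is scheduled at "Baseline, 3, 6, 12, 18 and 24 months".
- **Prognostic relevance** (Background): the article itself lists tumour location, stage and concomitant chemotherapy among the variables that influence swallowing outcome.

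**The concern.** The design balances the arms on factors that the article regards as influential, and then analyses the result as if allocation had been simple. It also measures the outcome instrument before treatment and does not use that measurement in the primary comparison. There are two separate consequences.

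1. **Baseline MDADI.** It is not a minimisation factor, so only the analysis can remove the noise that it contributes. With about 41 evaluable patients per arm, that noise widens the interval.
2. **Minimisation factors.** Forced balance makes the treatment difference less variable than the two-sample standard error assumes. If the factors are prognostic, that standard error is too large and the test rejects less often than 5% under the null.

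At stake are the width of the main confidence interval and the reserve of power if the SD or the evaluable number turns out worse than planned.

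**Working it through.** **Inputs from the article (Sample size):** difference 10 points, SD 13.8, two-sided 5%, power 90%, 41 per group, 20% drop-out, 102 recruited, 82 evaluable. **Assumed, because the article does not give them:** the baseline to 12-month correlation r, and the share R² of outcome variance explained by chemotherapy, site and stage.

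**Step 1. Reproduce the stated figure.** n = 2(1.960 + 1.282)² × (13.8/10)² = 40.02, rounded up to 41 per group. On the noncentral t distribution, n = 41.005 and power at 41 is 90.0%. Drop-out: 82/0.8 = 102.5, against 102 stated. The sample size is right for the unadjusted test.

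**Step 2. Adjust for baseline.** Residual SD = 13.8 × √(1 − r²). Half-width = t(0.975; 80 df) × SD × √(2/41), with t = 1.990. Unadjusted: 1.990 × 13.8 × 0.2209 = 6.07.

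| r (assumed) | Residual SD | Power at 41 per group | 95% CI half-width |
|---|---|---|---|
| 0 (unadjusted) | 13.80 | 90.0% | 6.07 |
| 0.1 | 13.73 | 90.3% | 6.04 |
| 0.3 | 13.16 | 92.5% | 5.79 |
| 0.5 | 11.95 | 96.3% | 5.25 |
| 0.6 | 11.04 | 98.2% | 4.85 |

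The degree of freedom spent on the covariate is ignored; with 80 available this is negligible. At r = 0.5 the unadjusted interval is 1/√0.75 = 1.15 times as wide.

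**Step 3. Error rate after minimisation.** Null trials were simulated with 102 patients, 22 centres, minimisation on centre, chemotherapy, site and stage (favoured arm chosen with probability 0.8) and about 82 evaluable. Each cell has 4,000 runs (Monte Carlo standard error about 0.3 percentage points). The two figures per cell are for r = 0 and r = 0.5. Centre was minimised on but given no effect on outcome.

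| R² (assumed) | Unadjusted t-test | Mann–Whitney | ANCOVA on factors and baseline |
|---|---|---|---|
| 0 | 5.4%, 5.2% | 5.2%, 5.0% | 5.0%, 4.3% |
| 0.1 | 4.0%, 4.7% | 4.3%, 4.4% | 4.6%, 5.1% |
| 0.2 | 3.5%, 3.6% | 3.7%, 3.3% | 4.8%, 4.8% |
| 0.3 | 2.9%, 3.4% | 3.0%, 3.4% | 5.5%, 5.2% |

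At R² = 0 the unadjusted figures agree with 5% within simulation error. Other simulations of the same kind gave 2.3% to 3.2% at R² = 0.3, so the end of the range depends on the settings.

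**Step 4. Power in the same simulations (1,500 runs per cell, 10-point effect).** The unadjusted t-test stayed at 90% to 93% throughout. The adjusted model reached 93.7% at R² = 0.2 with r = 0, and 98.6% at R² = 0.2 with r = 0.5.

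**The case against.** The strongest reply is that nothing here is wrong. The unadjusted comparison is unbiased over randomisation, the sample size was computed for that test, and it reproduces. Chance imbalance in baseline MDADI is already allowed for in the unadjusted standard error, so it is noise and not bias. All of this stands, and it limits the point to efficiency.

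The size of the gain also rests on values that the article does not give. At r = 0.1 the gain is 0.3 percentage points of power and 0.03 points of half-width, which is nothing in practice. This stands too, and is why a range is shown.

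Baseline is not ignored across the plan: a deterioration of 10 points or more is compared between arms, and the ANCOVA concerns change from baseline. Neither is the primary comparison, so this does not answer the point.

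A separate analysis plan may refine the method. But the article does not leave the primary test open; it names an unadjusted one.

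Finally, a model with several categorical factors and 20–25 centres on about 82 patients will have sparse cells, and the Mann–Whitney fallback for skewed scores needs a successor. Both are fair, and the fix deals with them.

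**Conclusion.** This is a worthwhile free improvement, not a defect that invalidates the trial. With baseline adjustment, power at 41 per group would rise from 90.0% to between 90.3% and 98.2%, and the half-width would fall from 6.07 to between 6.04 and 4.85 points, for assumed correlations of 0.1 to 0.6. Separately, if the minimisation factors explain 10–30% of variance, the unadjusted two-sided error is about 4%, falling to roughly 2.5–3%. If they explain nothing, it is 5%.

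A reader might infer more than the article supports:

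- **That false positives are inflated, or the trial is underpowered.** The departure is only in the conservative direction, and the planned 90% is met on the stated inputs.
- **That omitting baseline MDADI shifts the error rate.** It does not, because baseline is not a minimisation factor. It costs precision only.
- **That the error falls to 3.9%, 2.8% and 1.9% for R² of 0.1, 0.2 and 0.3.** The formula 2(1 − Φ(1.96/√(1 − R²))) gives these figures, but it presumes perfect balance on the factors among analysed patients. A random element and 20% loss loosen that balance.
- **That the Discussion's statement on pre-existing dysphagia is part of this error.** The Discussion says "Excluding patients with pre-existing dysphagia ensures that any post- treatment swallowing dysfunction is as a result of (chemo)-radiation treatment alone", whereas Table 1 excludes only "Documented evidence of pre-existing swallowing dysfunction (not related to HNC"). Tumour-related dysphagia is therefore not excluded by that criterion. This is a separate wording mismatch; here it adds only that baseline MDADI can be expected to vary.

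**What to change.** Prespecify the primary analysis as a linear model (ANCOVA) of the 12-month MDADI composite on:

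- treatment;
- baseline composite;
- chemotherapy use, tumour site/HPV and AJCC stage as fixed effects, with sparse categories pooled by a rule set in advance;
- centre as a random effect, since 20–25 centres share about 82 evaluable patients (82/25 to 82/20, or 3 to 4 each).

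Report the adjusted mean difference with its 95% CI. Keep the unadjusted t-test or Mann–Whitney test as a sensitivity analysis; the Mann–Whitney test then covers non-normal scores without a data-driven switch of the primary method. Correct the Discussion sentence separately so that it agrees with Table 1.

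The cost is a change of wording in the analysis section and the analysis plan, plus the pooling rule. No extra patients, visits or data are needed, and the target of 102 can stand. The change should be made before any outcome data are seen by arm, because adjustment chosen later would look data-driven.

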#### Statistical design

##### Sample size

In a previous cohort of patients treated with S-IMRT, mean MDADI composite score 12 months after treatment completion was 72 (SD = 13.8) [4]. A 10-point improvement in the MDADI composite score at 12 months is considered a clinically relevant outcome [40]. To have a 90 % power to detect this improvement (two- sided 5 % significance), 41 patients are required in each treatment group. Assuming a 20 % drop out due to disease recurrence, deaths and non-compliance with the 12-month questionnaire, the aim is to recruit 102 patients. MDADI compliance rates will be monitored regularly to ensure data on 82 evaluable patients are available.

Up to 50 of the recruited patients (25 in each arm) will additionally be included in the VF sub study. This will give 80 % power (one- sided significance 5 %) to detect an absolute difference of 33 % in the number of patients experiencing swallowing impairment according to the Penetration Aspiration Scale (based on 50 % in S-IMRT vs 17 % in Do-IMRT).

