The DARS trial recognises the importance of a comprehensive assessment for evaluating swallowing by including a multidimensional, longitudinal panel of functional outcome measures integrating instrumental, clinician- rated and patient- reported scales. The dashboard of swallowing measures adopted in DARS was developed in partnership with SLT leads from the PATHOS trial and should help the standardisation of future swallow outcome assessment and reporting. The MDADI composite score, the primary endpoint of DARS, is generated from a feasible and validated patient- reported swallow- specific questionnaire incorporating information from a patient’s physical, functional and emotional level at various recovery time points. Increasingly, it is being adopted as functional outcome tool for a number of head and neck cancer trials [44, 45].

The Do-IMRT is an adaptation of the planning methodology used by Feng et al. in that it will strive to spare the part of the pharyngeal constrictors lying in the elective target volume CTV_5400 rather than the medial RPN alone (Fig. 2) [46]. A theoretical risk of increased recurrence in the spared tissue exists with this approach. It is noteworthy that similar concerns were raised with the landmark parotid- sparing IMRT trial (PARSPORT), but these were proven to be unfounded when the data were analysed [19]. Furthermore, it is well established that the majority of the local recurrences following primary radiation- based treatment are in the immediate vicinity of the primary tumour site (GTV + 1 cm). Importantly, there will be no compromise of target coverage in this volume with Do-IMRT [47–50]. Therefore, the risk of recurrence in the spared tissue is perceived to be minimal. Nevertheless, the IDMC will closely monitor loco-regional recurrence rates and advise on early stopping of the trial if this is deemed necessary. Mean doses to the constrictors above 50 Gy have previously been shown to be associated with the risk of long-term dysphagia [18, 51], and have consequently been incorporated as the dosimetric constraint for the PCM within the study.

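### The primary analysis is called intention-to-treat but is an available-case comparison at 12 months, and unequal loss between arms would bias it in either direction

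*Protocol article*

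**What the plan says.** The Statistical analysis section of the protocol article fixes both the analysis set and the test. On the set: "The primary analysis will be by intention-to-treat, including all patients with 12 month MDADI data". On the test, the endpoint is to be "compared between the two groups using a two-sample *t*-test or non-parametric Mann–Whitney test, depending on distribution of the composite scores". Neither gives a score or rank to a randomised patient without a 12-month value.

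The Sample size section requires 82 evaluable patients, recruits 102, and explains the 20% difference as "drop out due to disease recurrence, deaths and non-compliance with the 12-month questionnaire".

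The Discussion says of the sparing technique: "A theoretical risk of increased recurrence in the spared tissue exists with this approach". It goes on to judge that risk minimal.

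Table 2 (Swallowing assessments) schedules the MDADI at "Baseline, 3, 6, 12, 18 and 24 months". The longitudinal MDADI pattern up to 2 years is a secondary objective (Study objectives and endpoints). Recurrence and survival are also compared by arm as secondary outcomes, and loco-regional recurrence is monitored for the IDMC (Interim analysis).

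**The concern.** Intention-to-treat means comparing all randomised patients in the groups to which they were randomised. The stated set keeps the allocation but also requires an observed outcome, and whether the outcome is observed is settled after randomisation. Two of the three reasons the plan gives for loss, recurrence and death, are bad outcomes. The plan also concedes that one of them could depend on arm. The patients compared at 12 months may therefore no longer be comparable by randomisation.

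At stake is the primary estimate. The trial aims to show better swallowing without worse disease control. If disease control were worse under Do-IMRT, some of the affected patients could leave the Do-IMRT mean and so raise the apparent swallowing benefit. The label would lead a reader to think the analysis is protected against this.

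A smaller point is efficiency. The primary comparison uses neither the baseline score nor the 3- and 6-month scores of patients who are missing at 12 months.

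**Working it through.** **1. The plan's own figures reproduce.** Inputs from Sample size: difference 10, SD 13.8, two-sided 5%, power 90%.

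n per arm = 2 × (1.960 + 1.282)² × (13.8/10)² = 40.02, rounded up to 41. The exact t-test power at 41 per arm is 90.0%. For drop-out, 82/0.8 = 102.5, against 102 stated. The sample size is not in error.

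**2. Patients outside the primary analysis.** 102 − 82 = 20, and 20/102 = 19.6%. The article does not split these 20 by arm or by reason.

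**3. Bias of the observed-case difference.** Let m be the share missing in an arm, and g the amount by which the missing patients' scores would lie below the observed ones. Then:

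- observed mean = mean of all randomised patients + m × g
- bias of (Do-IMRT − S-IMRT) = g × (m for Do-IMRT − m for S-IMRT), taking g as equal in the two arms.

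For a patient who has died, g is not a missing measurement. It is whatever score the analysis chooses to assign.

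**4. Illustration.** From the plan: 102 patients randomised 1:1 (51 per arm), 20 missing in total, SD 13.8. Assumed: the split of the 20, the value of g, and no true difference. Example: 20 × (13 − 7)/51 = 2.35 points.

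| Missing Do-IMRT / S-IMRT | g = 10 | g = 20 | g = 30 |
|---|---|---|---|
| 10 / 10 | 0 | 0 | 0 |
| 13 / 7 | +1.2 | +2.4 | +3.5 |
| 15 / 5 | +2.0 | +3.9 | +5.9 |

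Reversing a split reverses the sign.

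**5. Effect on the test at g = 20.** The chance of a false significant result favouring Do-IMRT is nominally 2.5%.

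- 13/7: standard error = 13.8 × √(1/38 + 1/44) = 3.06; the chance rises to about 11.5%.
- 15/5: standard error = 13.8 × √(1/36 + 1/46) = 3.07; the chance rises to about 24%.

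**6. Would the separate recurrence comparison reveal such an imbalance?** Not reliably. Suppose 4/51 against 8/51 events (assumed): Fisher's exact p = 0.36. With true rates of 8% and 16% (assumed), the power of that test is about 14%.

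**7. Information in the earlier scores.** Let ρ be the correlation between earlier and 12-month scores, and f the fraction of missing patients who have an earlier score. With 20% missing:

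ratio = (1/0.8) / [(1 − ρ²)/0.8 + ρ²/(0.8 + 0.2f)]

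- ρ = 0.6, f = 0.5: 1.25/(0.80 + 0.40) = 1.04
- ρ = 0.7, f = 1: 1.25/(0.6375 + 0.49) = 1.11

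The gain is 4% to 11% at these assumed values, before any gain from baseline adjustment.

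**The case against.** The strongest case on the other side has five parts.

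- **Recurrence is not an exclusion.** Only a missing score removes a patient. The drop-out sentence is a planning allowance, and nothing in the assessment sections stops MDADI collection at recurrence. This stands. A reader might infer that the plan drops every recurrence and so must flatter Do-IMRT, but the text does not say so. Only deaths are necessarily absent, and how they count is a choice of estimand.
- **The earlier scores are not discarded.** They serve the longitudinal secondary objective. This stands; they are unused only in the primary comparison.
- **The risk is judged minimal.** The Do-IMRT section rules out sparing within PTV_6500, and recurrence and survival are compared separately. This lowers the probability of a large imbalance and means a swallowing gain would be read beside the cancer outcomes. It does not change the primary estimate, and step 6 shows that a relevant imbalance could go undetected.
- **A repeated-measures model does not cure the problem.** Under missing at random it predicts 12-month scores from earlier ones, often recorded before recurrence. It also still needs at least one post-baseline score. This stands, so the model cannot be the whole remedy.
- **Sensitivity analyses usually belong in the SAP, which is not shown.** This is accepted, and their absence is not the finding. The finding is the analysis set, the test and the label that this text fixes.

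**Conclusion.** The point holds in a limited form. The primary analysis is an available-case analysis by allocated arm and should not be called intention-to-treat. By the plan's own figure it leaves out about 20 of 102 randomised patients, for reasons that partly reflect poor outcome.

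The direction of any bias is open. It favours Do-IMRT only if that arm loses more patients who would score worse, it runs the other way if S-IMRT does, and it is zero with equal loss of similar patients. A reader might infer that some overstatement arises even with equal loss. That would need the lost Do-IMRT patients to lie further below their own arm's observed mean than the lost S-IMRT patients do, and nothing in the document supports this.

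The possible size, about 1 to 6 points against the 10-point target, rests on assumed splits of 13/7 to 15/5 and assumed gaps of 10 to 30 points. It is enough to justify a change to the plan. It does not show that the result will be wrong, and it leaves the design and the sample size intact.

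**What to change.** 1. Describe the present analysis as available-case by allocation and keep it as supportive.
2. Make the primary estimate the 12-month difference from a repeated-measures model on MDADI at 3, 6 and 12 months. Include every randomised patient with any post-baseline MDADI, analysed as randomised. Adjust for baseline MDADI and the minimisation factors other than centre. Enter centre as a random effect or omit it, because 20–25 centres are too many fixed effects for 102 patients.
3. Because that model assumes missing at random and does not settle deaths, pre-state two companion analyses. In the first, patients who die or recur before 12 months and have no 12-month score take the worst rank. In the second, a tipping-point shift is applied to missing Do-IMRT scores.
4. Report missing 12-month scores by arm and by reason (death, recurrence, non-compliance).

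The cost is protocol and SAP wording and a little more analysis. No extra patients or visits are needed, since the scores are already scheduled. The downside is reliance on missing at random for the primary estimate, which the analyses in item 3 are there to test.
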